## Methods and analyses

The trial design is a two-group RCT to establish the effectiveness of an online self-help training and support program (iSupport) compared to an education-only comparison condition (EOC) which provides education about dementia and caregiving through an on-line e-book (Fig. 1). The objective is to examine the effect of this online self-help training and support program on depression and anxiety outcomes. The RCT will last 6 months in total, including pre measurement (T0), first follow up (T1, 3 months after T0) and second follow-up (T2, 3 months after T1). The timeline of assessments and measures are described in Fig. 2.

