**Fig. 1 Fig1:**
[figure not shown]
Flowchart of the iSupport Online Self-Help Program. T0 pre-measurement, T1 = first follow up 1–3 months post baseline, T2 second follow up: 2–6 months post T0

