### Outcomes

The primary outcomes are burden and symptoms of depression and anxiety (Table 1). Burden is measured by the 22-item Zarit Burden Scale [35]. Responses range from 0 (never) to 4 (nearly always). Depressive symptoms are measured using the modified version of the Center for Epidemiological Studies Depression scale (CES-D10): ten items measuring frequency of common depressive symptoms (e.g., sadness, hopelessness, sleep and appetite disturbances) in the past week. Response categories are: 0 (rarely or none of the time present) to 3 (most or all of the time present) [32]. Anxiety symptoms are measured using the General Anxiety Disorders scale (GAD-7), a 7-item measure rating the frequency of common anxiety symptoms (nervousness, worry, not being able to relax, being restless, annoyed or irritable, and feeling afraid that something awful will happen) in the past 2 weeks. Response categories are: 0 (not at all), 1 (several days), 2 (more than half the days) and 3 (nearly every day) [30].

**Table 1 Tab1:** Primary and secondary outcome measures and study variables in the iSupport online support trial

Outcome measures in the randomized controlled trial (RCT) (number of items, response scale, total scale score range)						
Primary	Target of scale	Reliability and validity of scales	Cronbach’s alpha	Pre measurement (T0)	First Follow up (T1)	Second Follow-up (T2)
Zarit Burden Scale (22, 0–4, 0–88)^a^	Perceived stress of caregiving	Intra-class correlation coefficient (ICC): 0.88 to 0.89	Cronbach’s α = 0.82 to 0.93	X		X
CES-D10 Center for Epidemiological Studies Depression Scale (10 items, 0–3, 0–30)^b^	Depression	Test-retest reliability (r values = 0.41 to 0.70)	Cronbach’s α = 0.80 to 0.85	X	X	X
GAD Generalized Anxiety Disorder 7-item scale (7 items,0–3, 0–21)^c^	Anxiety	ICC = 0.83	Cronbach’s α = 0.92	X		X
Secondary						
EuroQoL-5D Descriptive system of health-related quality of life states consisting of 5 dimensions (mobility, self-care, usual activities, pain/discomfort, anxiety/depression).^d^	Quality of Life	ICC = 0.70	No overall Cronbach's α reported		X	X
Mastery (7 items, 1–4, 7–28)^e^	Perlin 7-item Mastery Scale	Principal component factor loadings ranging from − 0.47 to 0.76			X	X
Self-efficacy (1, 0–5, 0–40)^f^	RIS Self-efficacy Scale	*r* = 0.48 to 0.69	Cronbach’s α = 0.72 to 0.79			X
Confounders/modifying Variables						

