### Statistical analyses

Analyses will be conducted according to the intention-to-treat principle. Randomization efficacy will be assessed by examining characteristics in the iSupport condition compared to EOC and missing data and unbalance will be evaluated. Missing data on follow-up measurements will be imputed using multiple imputations. To examine the association between the experimental and comparison group on the primary and secondary outcomes, we will first calculate paired *t* tests and estimates of effect sizes will be calculated. By using multiple regression analyses, we can correct for possible confounders. With a “generalized estimating equations” (GEE) analysis the research question regarding the maintenance of the effectiveness of the intervention will be answered for primary and secondary outcomes in separate models [41]. Thus, all primary and secondary outcome measures will be analyzed using separate GEE models using each separate outcome measure as the dependent variable and an indicator for the intervention (the iSupport intervention compared to the education-only control) as the primary independent variable. Potential confounders will be added to these models. All analyses will be conducted using SPSS for Windows.

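### The GEE cannot show a maintained effect for burden or anxiety, which have one follow-up each, and an arm main effect would not show it for depression either

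*Protocol article*

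**What the plan says.** The Methods and analyses section sets three visits, "including pre measurement (T0), first follow up (T1, 3 months after T0) and second follow-up (T2, 3 months after T1"), that is, at 0, 3 and 6 months.

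The Statistical analyses section first plans t tests and confounder-adjusted multiple regression for the group comparison. It then gives GEE its own task: "the research question regarding the maintenance of the effectiveness of the intervention will be answered for primary and secondary outcomes in separate models". The model follows as a consequence: one GEE per outcome, with "an indicator for the intervention (the iSupport intervention compared to the education-only control) as the primary independent variable". The only other terms named are confounders: "Potential confounders will be added to these models". Neither a visit term nor an arm-by-visit term is mentioned. The role of the baseline value, response or covariate, is not stated.

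In Table 1 (Outcomes section), the burden row, "Zarit Burden Scale (22, 0–4, 0–88"), and the anxiety row, "GAD Generalized Anxiety Disorder 7-item scale", are marked at T0 and T2 with T1 blank. CES-D10 is marked at all three visits. As the table was read, EQ-5D and mastery are marked at T1 and T2, and self-efficacy at T2 only.

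**The concern.** A claim that an effect was maintained needs an earlier effect and a later one to set against it. Burden and anxiety have a single post-randomisation measurement, so the data cannot tell an effect that arose early and lasted from one that arose late or has partly faded. An analysis plan cannot repair this, because the measurement is not taken.

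Where both follow-ups exist, the term put forward as the answer is a main effect of arm. That measures an average difference over visits, not its course.

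At stake is the interpretation. A significant arm coefficient for burden or anxiety could be reported as lasting benefit without support. Conversely, if the pre-randomisation visit is among the responses, a real 6-month effect would be shrunk and could be missed in this model.

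**Working it through.** **Inputs.** From the Sample size calculation section: effect 0.33 SD, two-sided alpha 0.05, 80 per group before dropout, endpoint ZBS change at 6 months. From Table 1: the visit marks above. From the Randomization section: baseline questionnaires precede allocation, so the expected arm difference at T0 is 0. Assumed, because the document gives no value: a common correlation r between visits, ranged from 0.3 to 0.7.

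**The plan's own figures.** 80 × 1.3 = 104 per group and 2 × 104 = 208, as stated. The 80 itself is not reproduced by a plain two-group comparison at 0.33 SD, which needs 145 per group. A baseline-adjusted comparison gives 80 only at r = 0.67, which the article does not state. That is a separate matter. Below, 80 and 0.33 are taken as printed.

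**Step 1: can maintenance be estimated?** Follow-ups after randomisation: burden 1, anxiety 1, depression 2. A T1-to-T2 contrast needs two. It exists for one of the three primary outcomes. Among the secondary outcomes, as the table was read, EQ-5D and mastery have two follow-ups and self-efficacy has one.

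**Step 2: does the arm term show maintenance for CES-D10?** With balanced arms and a common correlation, the expected arm coefficient is the mean of the visit-specific differences.

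- T0 among the responses, effect kept: (0 + 0.33 + 0.33)/3 = 0.22. Effect lost by T2: (0 + 0.66 + 0)/3 = 0.22.
- T0 not among the responses, kept: (0.33 + 0.33)/2 = 0.33. Lost: (0.66 + 0)/2 = 0.33.

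The two courses give the same coefficient either way. In a simulated GEE with T0 among the responses (400 runs per course, 80 per arm, r = 0.5, benefit coded negative), the arm coefficient averaged −0.225 for the kept effect and −0.235 for the lost one. The arm-by-T2 term separated them: −0.332 against 0.004.

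**Step 3: if T0 is a response row for ZBS and GAD-7.** Expected arm coefficient = (0 + 0.33)/2 = 0.165 SD, whatever r is. Power is Φ(z − 1.96), with:

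- arm only: z = 0.165/√(2 × ((1 + r)/2)/80)
- arm-by-time, same rows: z = 0.33/√(4(1 − r)/80)
- T2 adjusted for T0: z = 0.33/√(2(1 − r²)/80)

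| r | Arm only, T0 and T2 (0.165 SD) | Arm-by-time, same rows (0.33 SD) | T2 adjusted for T0 (0.33 SD) |
|---|---|---|---|
| 0.3 | 25% | 42% | 59% |
| 0.5 | 23% | 55% | 67% |
| 0.7 | 20% | 77% | 83% |

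At r = 0.8 the arm-only figure is still about 20% (z = 0.165/0.15 = 1.10). Simulation at r = 0.5 gave an arm-only coefficient of −0.159 with 22.5% power, and an arm-by-time coefficient of −0.333 with 56% power. The loss due to dilution alone is the difference between the first two power columns. The third column also includes the gain from baseline adjustment.

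**The case against.** **The model may be fuller than the article shows.** The arm indicator is called the primary independent variable, not the only one. T0 might enter as a covariate, and an analysis plan not shown here may name visit and interaction terms. This stands against any flat statement that the pre-treatment visit is averaged into the effect. A reader might infer that, because ZBS and GAD-7 without T0 have one record per person and nothing repeated for a GEE, but the article does not say it. The objection does not touch Step 1, since no model supplies an unmeasured T1 value.

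**The low power is not the power of the trial.** This stands. The group effect is also addressed by t tests and regression, the sample size rests on 6-month ZBS change, and r is assumed. The 20–25% belongs to one reading of one model.

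**Maintenance could just mean an effect still present at 6 months.** The article does not define the word, and T2 data can address that question for all three primary outcomes. If that is meant, it should be called the 6-month effect: a single follow-up cannot show that anything was kept.

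**Not every outcome is affected.** This also stands. CES-D10 and, as the table was read, EQ-5D and mastery have T1 and T2, so an arm-by-visit term would answer the question for them.

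**Visit timing.** A reader might infer from the Fig. 1 caption, "T2 second follow up: 2–6 months post T0", that the follow-up windows overlap and conflict with 3 and 6 months. The leading digits plausibly number the follow-ups (follow-up 1 at 3 months, follow-up 2 at 6 months), which agrees with the text. No conflict is established.

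**Conclusion.** The plan promises an answer on maintenance for all primary and secondary outcomes, and its measurement schedule cannot deliver it for burden and anxiety, two of the three primary outcomes. Self-efficacy is in the same position as the table was read. This rests only on the Table 1 marks. Because the table was extracted by a program and Fig. 2 is not shown, the column alignment should be checked against the published page.

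For CES-D10 the data suffice, but an arm main effect without arm-by-visit cannot tell a kept effect from a lost one, whether or not T0 is among the responses.

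The halving to 0.165 SD, with 20–25% power at 80 per arm, holds only if T0 is a response row and no arm-by-time term is fitted. It is a reason to state the role of T0, not a demonstrated flaw. The 6-month effect itself remains estimable for every primary outcome.

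**What to change.** 1. Limit the maintenance question to outcomes measured at both T1 and T2, and describe the burden and anxiety results as 6-month effects. This costs one sentence and a narrower claim. Alternatively, add ZBS and GAD-7 to the online T1 form for participants who have not yet reached it; the Trial status section says enrolment is under way. That costs 22 + 7 = 29 more self-report items at T1 and a change to a running study. T1 data would be incomplete, because those already past T1 would have none.

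2. Specify the GEE with post-baseline visits as the responses, the T0 value as covariate where it is collected, and arm, visit and arm-by-visit. Read the T2 contrast as the 6-month effect, and the T1 and T2 contrasts together for maintenance. For an outcome with T2 as its only follow-up, this reduces to a comparison at T2, adjusted for T0 where T0 exists. This is a change of wording and needs no new data.

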## Discussion

Dementia is a global public health priority. Especially in lower-resourced settings, a huge gap exists whereby there are not enough care providers and yet, there is a rapidly growing rate of dementia. Given this, risk reduction of dementia is important, as is the training and support for family and other caregivers to provide care to people who already have dementia or will have dementia. Family caregivers face significant challenges when providing care to people with dementia, putting them at greater risk for severe health problems, such as depression, anxiety and functional decline [27, 34, 42, 43].

In this RCT, we study the effectiveness of iSupport, an online training and support program. It is among the first of its kind adapted for a lower-resourced setting, delivered without the intervention of a health care professional, easily accessible via the Internet. In this trial, caregivers who use iSupport are compared to those who receive education only using the following outcomes: burden, and symptoms of depression and anxiety (primary outcomes); quality of life, person-centeredness, self-efficacy and mastery (secondary outcomes). The outcomes chosen for this trial have been used in several other trials related to Internet support and caregiver distress, internationally [14, 16–18].

There are some factors that may hinder participant inclusion for the trial. Firstly, online self-help training and the support program for caregivers are not commonly used and may not yet be readily accepted, particularly not by older caregivers in India. In general, receiving health information via the Internet in India is still relatively new. This may hamper the recruitment because caregivers tend not to automatically search for help on the Internet in general, which might also be exacerbated by the stigma related to dementia and to help-seeking [44]. This may also result in a relatively high dropout rate during the intervention period. Moreover, participants in the study may be younger (adult children) caregivers who are more familiar with the Internet as compared to older (spousal) caregivers. Another challenge is that the program is in English, and although many Indian people speak English, there is a low literacy rate (69.3% in 2011) [45] and it is certainly not the only language spoken in this country. This will result in the inclusion of a subgroup of caregivers that is highly educated [15, 46]. Another challenge may be that some households may not have reliable Internet coverage. Although this problem may decrease over time as the World Bank projects the greatest increases in Internet coverage to be in lower-middle income countries over the next few years, it may result in dropout during the study [47].

Anticipating challenges for inclusion and dropout, this study can be viewed as a first attempt to show the feasibility and potential of a self-help Internet-based training and support program for caregivers of people with dementia in a lower-resourced setting. A scalable approach is needed, given the large population of (adult child) caregivers of people with dementia, the urgent need for skills training and support to prevent and reduce caregiver distress, the growing number of Internet users, as well as the relatively low cost of such interventions [16, 18]. This also holds for other mental health interventions to reduce the mental health treatment gap [34, 48]. Internet-based interventions like iSupport may have potential for adaptation in differently resourced settings, and may help people with mental health problems around the world (Additional file 1).

## Trial status

The trial has completed initial planning and pilot testing. The trial is currently enrolling participants.

## Abbreviations

AD8: Alzheimer’s Disease Questionnaire-8-item
ARDSI: Alzheimer’s and Related Disorders Society of India
CES-D/CES-D10: Center for Epidemiologic Study Depression Scale
CTRI: Clinical Trials Registry—India
EOC: Education-only control
GAD-7: Generalized Anxiety Disorder scale-7-item
GEE: Generalized estimating equations
NIMHANS: National Institute of Mental Health and Neurosciences
RCT: Randomized controlled trial
T0: Pre measurement
T1: First follow-up
T2: Second follow-up
WHO: World Health Organization
ZBS: Zarit Burden Scale
